### Study outcomes

#### Primary outcome

The primary endpoint is a hierarchical composite of hospital mortality,
initiation of KRT, and ICU length of stay up to 28 days after randomization,
censored at hospital discharge. ICU length of stay is defined as the total
number of calendar days (without fractions) in the ICU from randomization to
hospital discharge.

#### Secondary outcomes

Secondary endpoints are hospital mortality, initiation of KRT, ICU-free days,
hospital-free days, vasopressor-free days, mechanical ventilation-free days,
and KRT-free days up to 28 days after randomization, censored at hospital
discharge. To be deemed vasopressorand mechanical ventilation-free, a cutoff
of 6 hours or less in an entire calendar day will be used.

Intensive care unit-free days, hospital-free days, vasopressor-free days,
mechanical ventilation-free days, and KRT-free days endpoints are defined as
the number of calendar days alive and free from each component, measured on
an ordinal scale from 0 to 29, with higher values indicating a better
outcome. A value of 0 will be assigned to participants who die prior to
hospital discharge. Participants who are discharged prior to Day 28 will be
assumed to be free of the endpoint through Day 28.

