#### Standard of care

Study sites and investigators will be expected to provide optimal management
for critically ill patients according to Brazilian and international
consensus and guidelines. This includes but is not limited to ventilation
support (oxygen, noninvasive ventilation, mechanical ventilation, among
others), hemodynamic support (vasopressors, inotropes), kidney replacement
therapy (hemodialysis, hemofiltration, hemodiafiltration, among others),
deep venous thromboembolism prophylaxis, delirium, sedation, and pain
management. All participant care except for study medication will be solely
determined by the local health care team.

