#### Study follow-up

Participants will be followed for 28 days or until hospital discharge,
whichever is sooner. The intervention group will be assessed for adherence
to the study drug daily from Days 1 to 14. For both the intervention and
control groups, adherence to mandatory laboratory parameters (serum
creatinine and blood gas analysis) will be assessed daily from Days 1 to
5.

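### KRT-free days credit a survivor who leaves hospital still on dialysis as KRT-free through Day 28, so a patient without kidney recovery can outrank one who recovered in hospital

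*Protocol article*

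**What the plan says.** Under Secondary outcomes, the protocol article defines each free-day endpoint as "the number of calendar days alive and free from each component", on "an ordinal scale from 0 to 29, with higher values indicating a better" outcome. Two scoring rules follow.

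- Death: "A value of 0 will be assigned to participants who die prior to" hospital discharge.
- Discharge before Day 28: the participant is "assumed to be free of the endpoint through Day 28".

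Both rules apply to all five free-day endpoints alike (ICU, hospital, vasopressor, mechanical ventilation and KRT). The only organ-support detail is a within-day cutoff "of 6 hours or less in an entire calendar day will be used", and it is given for vasopressors and ventilation, not for KRT.

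Three other sections bear on the point. Table 1 excludes end-stage kidney disease on maintenance dialysis. Study follow-up states: "Participants will be followed for 28 days or until hospital discharge", taking the earlier of the two. Planned Statistical Analysis puts KRT-free days into a Bayesian hierarchical ordinal model, with a Hodges-Lehmann difference as an exploratory summary.

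**The concern.** For ICU-free and hospital-free days, treating the time after discharge as free is true by construction, apart from readmission. KRT is different, because a patient can go home and continue dialysis as an outpatient. Maintenance dialysis is excluded at entry, so dependence at discharge is a new and unfavourable kidney outcome. The rule gives it the same credit as recovery. Follow-up ends at discharge, so no later observation corrects the score.

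Initiation of KRT is recorded as yes or no. KRT-free days is therefore the only listed outcome that can reflect how long KRT lasted. Survivors who never receive KRT all get the top score and deaths get 0, so among survivors the endpoint varies only through those who received KRT. An early discharge on dialysis puts a patient in the wrong place within that group, and both planned analyses depend on the ordering.

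**Working it through.** The protocol states no figure for this endpoint, so there is none to reproduce. The check applies the scoring rule to constructed patients.

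**Inputs from the protocol article**
- Calendar-day count, discharge rule and death rule: Secondary outcomes.
- 500 participants randomized 1:1, so 250 per arm; planned KRT initiation 10% (control) and 7% (dapagliflozin); planned hospital mortality 30% and 28%: Interventions, and Power and sample size.

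**Assumptions (not in the document)**
- KRT starts on Day 1, and scores are counted over Days 1-28. Moving to the 0-29 scale adds the same amount to every survivor compared here and changes no ranking.
- Every day from first KRT to discharge or recovery counts as a KRT day, including days between sessions. This reading is the less favourable one to the concern, so the discharge rule is tested alone.

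**Formulas**
- Dialysis-dependent, discharged on Day d, rule as written: 28 - d.
- Full recovery after n days of KRT: 28 - n.
- Dialysis-dependent, with dependence carried to Day 28: 28 - 28 = 0.

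| Dialysis-dependent, discharged on | Rule as written | Dependence carried to Day 28 |
|---|---|---|
| Day 10 | 18 | 0 |
| Day 14 | 14 | 0 |
| Day 21 | 7 | 0 |
| Day 28 | 0 | 0 |

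| Full recovery after | Score under either rule |
|---|---|
| 10 days | 18 |
| 12 days | 16 |
| 14 days | 14 |

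The patient discharged dependent on Day 10 (18) outranks those who recovered after 12 days (16) or 14 days (14). In general the order is wrong whenever d < n, that is, when the dependent patient leaves sooner than the other patient recovers. The rule adds 28 - d days, which is 18 days for discharge on Day 10 and none at Day 28.

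**How many participants**
- Planned initiators: 250 x 0.10 = 25 and 250 x 0.07 = 17.5, together 42.5 of 500 (8.5%).
- Initiators who die before discharge score 0 and cannot be misplaced by this rule. If initiators died only at the planned overall rates (an assumption), 25 x 0.70 = 17.5 and 17.5 x 0.72 = 12.6 would survive.
- The affected group is the part of these survivors discharged before Day 28 still on KRT. The document gives no rate for it, so the range runs from none to all of them.

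**The case against.** The strongest reply is that this is a disclosed simplification. The endpoint is labelled as censored at discharge, the text says openly that freedom is assumed, and the protocol describes organ support-free days, not kidney recovery. The rule is the same in both arms. KRT-free days is one of seven secondary endpoints, few participants are affected, and death supplies most of the variation: 250 x 0.30 = 75 and 250 x 0.28 = 70 participants per arm are expected at 0. All of this limits the stakes. It does not justify scoring a participant as free when the status at discharge is the opposite.

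A reader might also infer more than the document supports.

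- *Days between dialysis sessions are scored as free, so the endpoint tracks modality.* Standard of care lists "therapy (hemodialysis, hemofiltration, hemodiafiltration, among others", and both intermittent and continuous delivery are plausible, but the article never says whether a KRT day is a session day or a day within a KRT course. The analysis plan, which is not shown, may settle it. The choice matters. Take sessions on Days 3, 5, 8, 10 and 12 with dependent discharge on Day 13, against continuous KRT on Days 3-10 with recovery. Counting session days only gives 28 - 5 = 23 against 28 - 8 = 20, which is inverted. Counting Days 3-12 as KRT gives 28 - 10 = 18 against 20, which is correctly ordered. That example cannot carry the point.
- *All 17 to 25 initiators per arm are misplaced.* That figure includes those who die and those who recover.
- *One arm is favoured.* Nothing in the document fixes a direction. It would depend on how discharge timing and dialysis dependence differ between arms.

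**Conclusion.** The point holds for the discharge rule, which is explicit and has no exception for KRT. By itself it can place a survivor without kidney recovery above one who recovered, for example 18 against 16, where carrying dependence to Day 28 would give 0 against 16. The patient schedules are illustrative; the scoring rule is the protocol's own.

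The reach is narrow: survivors who start KRT and are discharged before Day 28 still on it, in numbers the document does not give. The net effect on the treatment comparison is therefore unknown in size and direction. The primary win ratio and the secondary outcome of KRT initiation use initiation as yes or no and are unaffected. The correction is worth making because it is cheap and because this is the only listed outcome that reflects KRT duration.

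**What to change.** 1. Add one field to the discharge form: *KRT ongoing at discharge (yes/no)*. Outcome data are already collected at discharge or Day 28 (Data collection and management).
2. For KRT-free days, except participants with a yes from the assumed-free rule and count them as on KRT through Day 28. Report the current rule as a sensitivity analysis.
3. In the same derivation, count days between intermittent sessions of an ongoing KRT course as KRT days, unless the analysis plan already does so. The discharge exception alone does not remove every inversion if only session days are counted. A never-recovered patient with three sessions a week has 12 session days in 28 and scores 16, above 14 for full recovery after 14 days of continuous KRT.

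The cost is one field, a derivation rule and slightly lower average KRT-free days. Status after discharge would still be assumed, not observed, because follow-up ends there. A participant who recovers soon after leaving would be scored too low, which is the reason to keep the current rule as the sensitivity analysis. Treatment, sample size and the primary analysis do not change.

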#### Safety outcomes

While meta-analyses of large placebo-controlled randomized trials of SGLT2
inhibitors found the use of this drug class to be generally safe, with a low
occurrence of diabetic ketoacidosis (0.3%)^(25)^ and no increased risk for acute kidney
injury, hypoglycemia, or hypotension,^(26)^ the DEFENDER study will be the first study
involving evaluation of the use of an SGLT2 inhibitor in critically ill
patients without COVID-19. Therefore, one of the key aspects of the study is
to closely monitor for potential adverse events.

All serious adverse events will be promptly reported by the study sites.
Additionally, we will collect information on adverse events of special
interest, including liver transaminase elevation (greater than three times
above the reference range), skin lesions, hypoglycemia, urinary tract
infection, bloodstream infection, and diabetic ketoacidosis, irrespective of
their severity and causality assessment. Participants will receive
dapagliflozin in a strictly monitored environment, which enables the timely
identification and management of potential adverse events. Acid‒base
disorders and kidney function will be monitored during the first five days
of study follow-up.

### Statistical considerations

#### Planned Statistical Analysis

The primary outcome analysis will be conducted using the unmatched win ratio
(WR) method^(27)^ as
proposed by Pocock et al.,^(28)^ with the hierarchical composite primary outcome of (1)
hospital mortality, (2) initiation of KRT, and (3) ICU length of stay-LOS
(in days). The win ratio will be assessed by comparing every possible pair
of participants from the intervention and control groups in a pairwise
descending fashion. A structural framework using nodes in a decision tree
will be used for each level of comparison, with labels of “win” or “loss”
assigned if one participant has a better outcome than the other or a “tie”
otherwise. Hospital mortality will be the primary level of comparison, and
reflecting the higher importance of this outcome, pairwise comparisons in
which both participants die will be determined as an early “tie.” If both
participants survive, they proceed to the second level of the hierarchy for
a comparison of the initiation of KRT. If both participants do not require
KRT, or if both require it, the pair is then moved to the third level to
compare the ICU LOS. For the ICU LOS outcome, the pair with the shorter
duration of stay is considered the “winner.” The structural framework for
the three pairwise comparisons according to the hierarchy of the composite
primary outcome is shown in figure 2.

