### Study procedures

#### Interventions

Eligible patients will be randomized 1:1 to dapagliflozin 10mg plus standard
of care or standard care alone (Figure 1). Randomization is performed centrally through the Research
Electronic Data Capture (REDCap) system,^(24)^ stratified by study site with variable
block sizes of 4, 8 and 12. A confidential randomization list was generated
by the coordinating center. As an open-label study, no procedures to blind
site staff, study personnel, or physicians involved in patient care will be
conducted.

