#### Data collection and management

Trained research personnel from study sites will use the REDCap system to
collect data. Data on eligibility criteria that are not met will be
collected as screening logs. At randomization, demographic information,
comorbidities, concomitant medications, reason for ICU admission, and
illness severity will be collected. Daily data collection will include
information on treatment adherence, blood gas analysis, and serum
creatinine. Blood gas analysis forms will contain ranges of possible values
for pH, bicarbonate, and base excess. Information regarding study outcomes
will be collected on Day 28 or at hospital discharge. Serious adverse events
and adverse events of special interest will be collected throughout the
study.

To ensure data quality and confidentiality, investigators and study staff
will receive training on data collection, including a dedicated training
environment in the electronic data capture system that will register
deidentified information about study participants. The coordinating center
will check the data weekly, and study sites will receive a monthly report on
data quality. On-site and remote monitoring will be conducted during the
study. We plan to recruit 500 participants in at least 20 Brazilian
ICUs.

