**Figure 2 f2:**
[figure not shown]
Flowchart for the win ratio according to the hierarchy of the
primary outcome.

The WR is calculated as the ratio of the total number of “wins” between the
intervention and control groups, and a WR > 1.0 indicates a better
outcome in the intervention group. The 95% confidence intervals (95%CI) for
the WR will be calculated by bootstrapping based on 10,000 samples, and
95%CI not including the unit (1.0) will be considered statistically
significant.

Secondary binary outcomes will be analyzed using a Bayesian hierarchical
logistic regression model. The model will include the study group as a
predictor and will be adjusted for study site, age, clinical suspicion of
sepsis, use of vasopressors, and mechanical ventilation at randomization. A
neutral prior of moderate strength^(29)^ and normal distribution, centered at an odds ratio
(OR) of 1.0 and a standard deviation of 0.35, corresponding to a 95%
probability that the effect (OR) is within the 0.5 - 2.0 range, will be
used. Superiority of the dapagliflozin group over the control group will be
determined if the posterior distribution of the adjusted odds ratio (aOR)
being less than 1.0 [Pr (aOR < 1.0)] is more than 95%. The results will
be presented as the posterior distribution of the aOR (in log scale), a 95%
credible interval, and the probability of the aOR being less than 1.0.

Intensive care unit-free days, hospital-free days, vasopressor-free days,
mechanical ventilation-free days, and KRT-free days will also be analyzed
using a Bayesian hierarchical ordinal model, using the same covariates from
the binary outcomes model. Frequentist analysis exploratory analysis for
secondary outcomes will also be performed, and no p values will be
presented. Binary outcomes will be analyzed thorough a logistic regression
model, with the same covariates as the Bayesian models, and data will be
presented as aOR, crude OR, and corresponding 95%CI. Treatment differences
in free day outcomes will be calculated using the Hodges‒Lehmann method and
presented as the difference in days and 95%CI.

All primary, secondary and safety analyses will follow the intention-to-treat
principle. A sensitivity safety analysis will also be conducted in all
participants who received at least one dose of dapagliflozin (safety
population). Full details of all planned analyses are provided in version
1.0 of the Statistical Analysis Plan (Supplementary Material). All analyses

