#### Subgroup analysis

For the primary and secondary outcomes, the following relevant subgroup
analyses were planned: clinical suspicion of sepsis at randomization
(yes/no), diabetes mellitus (yes/no), serum creatinine at enrollment (<
1.5mg/dL, 1.5 - 3.0mg/dL, and > 3.0mg/dL), cardiovascular reason for ICU
admission (yes/no), and age (< 65 and ≥ 65 years). Stratified WR
analysis will be performed for each subgroup stratum. The 95%CIs will be
calculated by bootstrapping 10,000 samples for each analysis, and 95%CIs not
including the unit (WR = 1.0) will be considered statistically significant.
We will also perform additional analysis for the secondary outcomes within
each subgroup using the same Bayesian models and exploratory frequentist
analysis.

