#### Power and sample size

We estimated that a sample size of 500 participants would provide at least
85% power to detect a win ratio and corresponding 95%CI above 1. This
calculation was made based on the following assumptions: (1) a 2% absolute
reduction in hospital mortality from 30 to 28% with dapagliflozin; (2) a 3%
absolute reduction in initiation of KRT from 10 to 7% with dapagliflozin;
and (3) a mean reduction in ICU LOS of 0.5 days with dapagliflozin. The
estimation was obtained after performing 10,000 simulations in samples of
500 participants using these assumptions and 95% confidence intervals
obtained by bootstrapping. Figure 3
displays the results of the obtained lower boundaries of the 95% confidence
intervals of the win ratio values from these simulations.

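### The primary win ratio is valid but unadjusted; prespecifying adjustment for covariates the plan already uses, and adding baseline creatinine to the KRT model, is a cheap gain in power

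*Protocol article*

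**What the plan says.** All references are to the protocol article.

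- **Primary analysis** (Planned Statistical Analysis): "The primary outcome analysis will be conducted using the unmatched win ratio". "The win ratio will be assessed by comparing every possible pair" of treated and control participants, on hospital mortality, then KRT initiation, then ICU length of stay. The interval comes from 10,000 bootstrap samples, and a "95%CI not including the unit (1.0) will be considered statistically" significant. No covariate or stratum is named.
- **Secondary analyses** (same section): the Bayesian logistic model has study group as a "predictor and will be adjusted for study site, age, clinical suspicion of" sepsis, vasopressor use and mechanical ventilation at randomization. The ordinal free-day models use the same covariates. The prior on the log odds ratio is normal, centered on no effect, with SD 0.35.
- **Allocation** (Interventions): randomization is 1:1, "stratified by study site with variable" block sizes.
- **Other baseline data**: Data collection and management says that at randomization "illness severity will be collected". Subgroup analysis lists "diabetes mellitus (yes/no), serum creatinine at enrollment" among its factors. Neither creatinine nor a severity measure is in the covariate list.
- **Power** (Power and sample size): "We estimated that a sample size of 500 participants would provide at least" 85% power, from simulations whose description mentions no covariates.

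The WR analysis described under Subgroup analysis is a separate WR in each subgroup stratum, not an adjusted primary. Fuller analysis details are left to the SAP, which is not at hand.

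**The concern.** By listing age, suspected sepsis, vasopressors and ventilation in the models for mortality and KRT, the plan treats them as prognostic for the two outcomes that rank first and second in the primary. Yet the one test with a significance rule does not use them. Chance imbalance in these factors then passes into the WR, and its interval is wider than the collected data would allow.

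The covariate list itself also misses something. Creatinine at enrollment is an obvious candidate predictor of starting KRT. It is recorded, but used only to form subgroups.

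At stake is power. The assumed effects are small: 2 points in mortality, 3 points in KRT and 0.5 days in ICU stay.

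**Working it through.** **1. The plan's own power figure.** Inputs from Power and sample size: 250 per arm, mortality 30% vs 28%, KRT 10% vs 7%, ICU stay shorter by 0.5 days on average. The article gives no SD or distribution for ICU stay, so the 85% can be neither reproduced nor refuted. The hierarchy was simulated 1,000 times per setting, with a large-sample SE of log WR in place of the bootstrap and an assumed mean stay of 7 or 10 days. Two-sided power was:

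| Assumed SD of ICU stay (days) | Power |
|---|---|
| 0.75 | 92% |
| 1 | 81-83% |
| 2 | 41-46% |
| 3 | 34% |
| 5 | 20-28% |

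So 85% needs an SD of roughly 0.9-1 day. Below, 85% is taken as the starting value and 25% as a pessimistic alternative.

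**2. Variance reduction from adjustment.** The documents give no prognostic strength, so it is an assumption. Trials of 500 were simulated with overlap weights or comparable adjustment on four covariates, under three sets of assumptions:

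| Assumed prognostic strength | Fall in variance of log WR |
|---|---|
| Mortality AUC about 0.65, 0.69, 0.72 | 4%, 8%, 12% |
| Mortality AUC 0.65, 0.69, 0.73; covariates also predict ICU stay | 10%, 17%, 21% |
| Three increasing strengths; covariates also affect ICU stay | 5%, 16%, 22% |

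In the second set the mean log WR, unadjusted vs adjusted, was 0.139 vs 0.139, 0.137 vs 0.135 and 0.129 vs 0.131. The effect being estimated hardly moves; the variance falls.

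**3. Translation into power.** If adjustment removes a share r of the variance:

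power = Φ[(1.960 + z_P)/√(1 − r) − 1.960], where P is the unadjusted power; effective N = 500/(1 − r).

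For P = 85%, 1.960 + 1.036 = 2.996.
- r = 0.04: 2.996/√0.96 = 3.058; 3.058 − 1.960 = 1.098; power 86.4%; effective N = 521.
- r = 0.22: 2.996/√0.78 = 3.393; 3.393 − 1.960 = 1.433; power 92.4%; effective N = 641.

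For P = 25%, 1.960 − 0.6745 = 1.2855.
- r = 0.04: 1.2855/√0.96 = 1.312; power 25.9%.
- r = 0.22: 1.2855/√0.78 = 1.456; power 30.7%.

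A separate simulation of a covariate-adjusted rank analysis of the same hierarchy agrees. With an ICU-stay SD of 1 day and 11% of variance explained, power rose from 82% to 86%. With an SD of 5 days and 5-11% explained, it rose from about 26% to 28-29%.

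**4. Creatinine in the KRT model.** At 10% vs 7% with 250 per arm, 25 and 17.5 events are expected.

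SE of the crude log OR = √(1/25 + 1/225 + 1/17.5 + 1/232.5) = √0.1059 = 0.325.

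Data precision is 1/0.1059 = 9.44; prior precision is 1/0.35² = 8.16. The prior therefore carries 8.16/(8.16 + 9.44) = 46% of the total, which damps any gain. Judged by squared z values from a model without the prior, adding creatinine is worth 6-23% in effective sample size (assumed AUC 0.71-0.83). Under the planned prior it is worth about 2-9% (assumed AUC 0.71-0.82). The gain is in power: a prognostic covariate moves the conditional log OR away from zero and does not shrink its SE.

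**The case against.** The strongest reply is that nothing here is wrong. An all-pairs WR is valid under randomization, comes with its interval and decision rule, and matches the power simulation as described. Adjusting secondary regression models does not contradict an unadjusted primary. All of that stands: the point is an improvement, not a correction.

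Three stronger readings are tempting and should not be drawn.

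- **A reader might infer that the models ignore illness severity.** They do not. Vasopressor use and mechanical ventilation at randomization are severity markers. What is absent is the recorded severity measure and a renal marker, and the added value of the severity measure beyond the listed covariates was not computed.
- **A reader might infer that the bootstrap ignores the site-stratified allocation.** The article does not state the resampling unit, and the unseen SAP may. Nor is there a demonstrated gain from comparing only within site: in simulation with 22 sites of about 23 participants, that raised the variance by 5-7%.
- **A reader might infer that adjustment would secure the stated power.** Step 3 shows otherwise: if power is really about 25%, it becomes 26-31%.

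Two practical objections also carry weight. The trial is open-label and enrolling, and the safety board has seen unblinded data, so a change to the primary must be made by people without access to outcomes by arm. And only about 42 KRT events are expected, in a model that already has at least 20 ICUs and four other covariates, so the list should not grow freely.

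**Conclusion.** The point holds as a cheap improvement. The article fixes an unadjusted primary and a covariate list that serves only the secondary models, so this is more than detail left to the SAP, although the SAP may already contain a supportive adjusted analysis.

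The gain for the WR is a 4-22% fall in the variance of log WR. Its direction agreed across all simulations; its size rests on assumed prognostic strengths, and the 86-92% power also rests on a true starting value of 85%. The gain for the KRT model is smaller, about 2-9% in effective sample size. The missing SD of ICU stay matters far more to the power claim than either, and is a separate matter.

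**What to change.** Before data lock, and without reference to outcome data by arm:

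1. **Prespecify a covariate-adjusted WR** using at least age, suspected sepsis, vasopressor use and mechanical ventilation at randomization. One way is to weight pairs by overlap weights from a logistic model of allocated arm on these covariates, refitted in every bootstrap sample. Always report the unadjusted WR beside it.
2. **State which of the two carries the significance rule.** The power gain reaches the primary test only if the adjusted WR is named primary. If that can no longer be decided blind to outcomes by arm, keep it as a supportive analysis.
3. **Add log baseline creatinine to the secondary models**, chiefly KRT initiation, and the recorded illness-severity measure if it is complete.
4. **Fix a simple rule for missing baseline values**, applied identically in both arms.

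The cost is amended analysis wording, modest R code and a slightly more complex analysis. No extra participants or data items are needed.
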